### Institutional Review Board approval and informed consent

The trial has been reviewed and approved by the institutional review board (IRB) of the University Medical Center Utrecht (The Netherlands). Furthermore, local IRB approval has been obtained in the participating centers for the local applicability of the protocol. Details regarding the IRB approval are presented in Additional file 4. Written informed consent will be obtained from all patients.

### Risk assessments

The treatment algorithm introduced in the patients assigned to EGDT includes measurement of cardiac output, SVV, and PLR as a test. These measurements are performed using the arterial catheter, which is routinely placed in patients undergoing high-risk, non-cardiac surgery. Therefore, no additional catheters are placed in comparison with routine hemodynamic monitoring. EGDT involves fluid therapy and inotropic support, which are commonly used in patients undergoing high-risk surgery. Additional risk associated with its use in the treatment algorithm is therefore not likely in comparison with routine practice. The systematic review of the literature performed before this study (Additional file 1) reported adverse events due to the use of pulmonary artery catheters, which are not used in this study. Only one study reported myocardial ischemia due to use of inotropic support, which disappeared after stopping inotropic infusion [6]. In the other studies however, the results point to a lower incidence of myocardial ischemia, although significant reductions have not been reported. Adverse events with respect to fluid overload have not been described in the systematic review. Despite this, precautions have been taken in the EGDT algorithm to prevent the potentially harmful effects of excessive fluid and inotropic support.

### Safety procedure

Events that meet the criteria for ‘severe adverse events’ (SAE’s) are monitored and reported to the accredited IRB that approved the protocol and to a Data Safety Monitoring Board (DSMB). The major complications embedded in the primary outcome measure meet these criteria and are considered ‘expected SAE’s’. Cumulative data on these expected SAE’s are reported biannually. Mortality and all other ‘unexpected SAE’s’ are reported immediately. The DSMB has been created to assess the safety of the interventions and to monitor the overall conduct of the study. In addition, the DSMB assists and advises the investigators in protecting the validity and credibility of the trial. The members of the DSMB for this trial are an epidemiologist and biostatistician, an anesthesiologist and intensivist, and a gastrointestinal surgeon. The DSMB members will meet every six months in closed and open sessions. After each meeting the DSMB may decide the following: the trial is allowed to continue without further action, the trial is allowed to continue with recommendations which will be evaluated in the next meeting, or recruitment of patients is stopped since accumulating data points to an adverse effect in the intervention arm. The study will not stop if accumulating data points to a beneficial effect in the intervention arm. The roles and responsibilities of the DSMB are described in detail in a DSMB charter.

## Discussion

### Trial context

There is an urgent need for a multicenter, randomized controlled trial, evaluating the application of AWA-based hemodynamic monitoring in goal-directed strategies for high-risk surgical patients [14, 34, 35]. Ideally, the algorithm used for EGDT should be user-friendly and easily applicable in order to enhance the implementation in daily care. Moreover, this trial should include a large group of patients in order to have sufficient power to demonstrate differences in clinically relevant outcome parameters. Finally, long-term effects in terms of QOL and healthcare costs should be considered. So far, this ‘ideal’ trial has not been performed. The presented study protocol attempts to include the important features mentioned, however, a number of aspects of the trial design however need to be discussed in detail. First we try to elucidate the clinical choices made in the selection of patients, the EGDT algorithm, care in the control group, and safety. Next, we will discuss a number of methodological issues with respect to the study design, primary outcome measure, blinding, and discharge criteria.

### Clinical considerations

#### Patient population

Each year a large number of patients are scheduled for extensive abdominal surgery in a variety of hospitals. The postoperative problems seen in the postoperative period involve a major burden to patients and healthcare costs, and are acknowledged by many clinicians in the field of anesthesia, critical care, and surgery. Yet there is ongoing debate if and which type of advanced hemodynamic monitoring should be applied in these patients. In contrast, transesophageal echocardiography and pulmonary artery catheterization are extensively used in patients undergoing cardiac surgery, while the risk for postoperative complications or mortality is often lower. Therefore, we chose major abdominal surgery as the target population in this study. Hepatic resections are considered high-risk abdominal surgery, especially due to bleeding complications. Intraoperatively, however, the use of fluids is highly restrictive and the algorithm described in this study is not suitable for application in this specific patient category. Therefore, we decided to exclude patients scheduled for hepatic resection.

#### EGDT algorithm

The algorithm was designed to be as easy as possible, to enhance the applicability in the various types of hospitals performing high-risk abdominal surgery. Basically, the algorithm includes three steps: 1) detect a drop in CI below the target value, 2) determine the intervention to restore the CI, and 3) evaluate if the CI increases above the target value.

The AWA technique used is not prescribed, but depends on the preference of the hospital. This will enhance the willingness to implement EGDT in clinical practice, since many hospitals already have AWA monitoring systems for other clinical purposes. In addition, EGDT is the intervention under investigation, not a specific device. AWA algorithms continue to improve and new devices will emerge in the coming years [36, 37].

We decided to use CO, indexed to Body Surface Area (BSA(m^2^) = 0.20247 × Height(m)^0.725^ × Weight(kg)^0.425^), as the target variable in the EGDT algorithm. CO gradually decreases with increasing age [38, 39]. Since age varies considerably in the target population, we decided to use different target CI values in three age categories. Assessment of fluid responsiveness is the first step in optimizing CO. An SVV measurement can be used for this purpose, if a number of criteria for mechanical ventilation are met [14, 15]. In the OR, this will be the case in most situations. In the ICU or PACU however, patients are weaned from the ventilator, which hinders the reliability of dynamic preload assessment. In these circumstances, PLR testing provides a suitable alternative, if properly performed [24–26]. If the SVV criteria are not met and PLR testing is not possible, we decided to use a small FC to prevent unwanted volume loading in unresponsive patients. This small FC can be repeated if the patient responds well. Otherwise, inotropic support is used to restore the CI. Overall, SVV and PLR testing are important in the algorithm, which emphasizes the role of cardiac preload in treating low CO. Preload optimization is, however, not the primary target in this trial, since CO represents the most direct way to determine tissue oxygen delivery in the perioperative period [13].

Central venous oxygen saturation (S_cv_O_2_) has been shown to be effective as a target variable in a number of goal-directed strategies in critical care, and has been considered as target variable for this trial as well [40–43]. There are, however, a number important limitations. For proper interpretation, oxygen consumption should be considered, which varies in the perioperative period to a great extent [40]. In addition, S_cv_O_2_ is usually intermittently determined, since special oximetry probes are needed for continuous S_cv_O_2_ measurement. Therefore, S_cv_O_2_ was not chosen as target in the treatment algorithm, but may be used additionally according to local practice.

The EGDT algorithm starts in the OR after induction of anesthesia before the start of surgery. Postoperatively in the ICU/PACU, EGDT continues until discharge for a maximum of 24 hours. In most hospitals, it is common practice to monitor patients after high-risk surgery for this period. For practical reasons therefore, EGDT can easily be implemented. More importantly, impaired tissue oxygenation may present up to 24 hours after surgery [44–46].

#### Standard care

We decided to limit the criteria for standard care in order to keep care in the control group close to local routine. As described above, EGDT is meant as a supplement to standard care, not as a substitute. For reasons of generalizability to other institutions, care in the control group should not deviate from local routine to a great extent. On the other hand, bias or major differences between the participating centers may occur if standard care is rather heterogeneous. Criteria for mechanical ventilation were introduced to prevent bias from differences between the groups, since a reliable SVV measurement requires specific ventilation settings [14, 15]. The other criteria are very routine in most institutions. The use of epidural analgesia, enhanced recovery after surgery (ERAS) protocols, corrections for preoperative fasting, and basic fluid regimes are not obligatory. Due to randomization, these treatment elements are expected to be balanced between the control and intervention groups. In addition, these elements do not interfere with the application of EGDT.

It would be valuable to monitor CO in the control group as well, albeit blinded for the clinicians. The presence or absence of differences in outcome between the control and intervention group are easier to interpret in the light of differences in CO between the groups. In clinical practice however, it may be difficult to apply standard care in the control group in the presence of a CO monitor. We fear that clinicians may tend to take CO values into consideration in their therapy. In addition, CO monitoring is associated with significant costs, which increases the total costs of the trial to a great extent.

#### Safety

Our systematic review of the literature did not reveal any harm due to the use of fluid or inotropes in goal-directed strategies. In the OR and ICU/PACU, both fluid and inotropes are extensively used. We decided to allow the use of both crystalloid and colloid fluids, according to local preferences. Norepinephrine and dobutamine were chosen for inotropic support as these inotropes are commonly used. Clinicians and other healthcare personnel are therefore familiar with the administration, clinical effects, and adverse reactions. In the algorithm however, patients may end up in a continuing loop of fluid or inotropic support if the response in CI is insufficient. In this case, volume overloading or adverse effects of inotropes may occur, and a number of safety measures have been incorporated in the algorithm in order to address this. If tachycardia, arrhythmia, myocardial ischemia, pulmonary edema, or cardiac decompensation is suspected or observed, any intervention within the algorithm should be stopped immediately. In contrast, fluid or inotropes should not be withheld in patients with CI values above their target. We therefore emphasize that EGDT is added to standard care and does not replace it. Interventions within the usual care for high-risk surgical patients, such as treatment of hypotension, hypovolemia, or any other suspicion of hemodynamic deterioration, should therefore be applied irrespective of the CI or the treatment algorithm.

### Methodological aspects

#### RCT design

Especially in studies evaluating perioperative hemodynamic therapy, randomized controlled trials (RCTs) have a number of limitations, such as impossibility to blind at the patient and caregiver level, and the Hawthorne effect [34, 47, 48]. The Hawthorne effect is a phenomenon whereby clinicians tend to improve care for patients included in studies, which may affect outcome in both the control and intervention groups [49]. We discussed the alternative approach of a before-after study. For the purposes of our study, prospective data collection is necessary. Therefore, the Hawthorne effect will be present in both ‘before’ and ‘after’ periods. More importantly, postoperative outcome after high-risk surgery is multifactorial. It is simply impossible to keep all these factors constant during the entire study period, which was the main reason for choosing the RCT design. Since the start of our trial, a number of important aspects in the care for high-risk surgical patients have changed. First, robotic surgery is increasingly being used in our institutions. Second, surgical safety checklists have been introduced in many centers, reducing both mortality and morbidity after surgery [50]. In one of the participating centers in this trial this led to a significant reduction in 30-day in-hospital mortality [51]. Similar checklists have been implemented in the other participating centers. We therefore regarded randomization to be crucial in this study. We stratified the randomization procedure with respect to participating center and type of surgery, since these covariates may influence outcome to a great extent. The number of patients in certain strata may become small however, which was the reason for applying blocked randomization.

#### Primary endpoint

The primary outcome measure in this trial is a combined endpoint of major complications in the first 30 days after surgery, including mortality. The use of composite endpoints in trials is common in order to increase statistical power and to capture the net benefit of the intervention [52, 53]. The most important disadvantage of this approach is that interpretation of the results is difficult if the outcomes are of different importance to patients. The components of a composite endpoint should therefore be clearly defined, clinically important, effected by the intervention, as homogeneous as possible, and weighed to reflect their relative importance [53].

The major complications embedded in the composite endpoint in our study are clearly defined and associated with increased long-term morbidity and mortality. Yet there are differences in terms of clinical consequences for the patient. Therefore, we decided to take the number of complications per patient as a primary endpoint, instead of the number of patients with one or more complications. In this way, the severity of the complication is reflected. For instance, if a patient develops pneumonia, which is treated with antibiotics in the ward, there is only one complication registered. If the patient however needs ICU readmission because of respiratory failure and septic shock, three complications are registered. We will report all complications separately to show if a difference in the primary endpoint is predominantly caused by one or more specific complications. In addition, the complications will be weighed using the Accordion complication severity score [31].

A number of other outcome measures have been considered as a primary endpoint in this trial. First, we performed a sample size calculation for the detection of a difference in mortality. This however revealed that over 5,000 patients would be needed, which was not feasible. Second, we calculated that approximately 250 patients would be needed to detect a difference in length of stay in the hospital. As a result, the study would have insufficient power to detect differences in terms of morbidity, which was our primary aim. Third, a single complication taken as an outcome measure was considered. In this case, however, consequences for the patient may differ considerably as well. As described previously, pneumonia may have a mild clinical course, but may also result in septic shock with multi-organ failure. Finally, we considered complications weighed according to the Accordian complication severity score as a primary outcome measure [31]. This, however, requires an ordinal approach to data-analysis, which is not straightforward. In addition, it remains difficult to compare patients with multiple complications.

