## Background

### High-risk surgery

Both the extent of the surgical procedure and the presence of comorbidities increase the risk of an adverse outcome after surgery. Moreover, approximately 12.5% of all surgical patients are considered as ‘high-risk’ [1, 2]. The majority of perioperative complications and death occur in this minority of patients [1]. With increasing age and comorbidities in the general population, the number of high-risk surgical patients is expected to grow. Approximately 50% of these surgical patients develops one or more perioperative complications, and mortality in this specific patient group is around 5% [1–6]. Major complications such as myocardial infarction, cardiac failure, stroke, pneumonia, renal failure, or sepsis, involve a significant burden to the patient and to hospital facilities during the hospitalization period [3]. After discharge, these complications may result in long-term disability, cognitive impairment and even death, significantly reducing quality of life and increasing healthcare consumption [3].

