### Outcome measures

The primary outcome measure is the number of major complications per patient within the first 30 days after surgery, including mortality. An overview of all major complications can be found in Table 2. The complications within this composite endpoint are associated with increased long-term morbidity and mortality [3].

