**Table 2 Tab2:** **Major complications within the first 30 days after surgery embedded in the composite primary endpoint**

Category	Complication	Criteria
Mortality	30-day mortality	Mortality within the first 30 days after surgery
Cardiovascular	Cardiac arrest	Cardiac arrest, electromechanical dissociation, ventricular fibrillation, or ventricular tachycardia without output
	Acute myocardial infarction	According to the criteria for acute myocardial infarction (see Universal Definition of Myocardial Infarction [27])
	Acute pulmonary edema	Diagnosis confirmed by X-ray
	Stroke	Focal brain injury that persists for >24 hours, combined with an increase in disability of at least one grade on the modified Rankin scale [28], confirmed by cerebral CT-scan
Respiratory	Prolonged mechanical ventilation	Postoperative mechanical ventilation for more than 24 hours (any cause), including non-invasive pressure support ventilation through a face-mask
	Pulmonary embolism	Confirmed by CT-scan
	Pneumonia	Confirmed by X-ray and treated with antibiotics
	Respiratory failure	Any other respiratory complication requiring mechanical ventilation (including non-invasive pressure support ventilation)
Renal	Acute kidney injury	Stage 2 or 3 acute kidney injury, according to the Acute Kidney Injury Network [29]
Gastrointestinal	Anastomotic leak	Diagnose made and confirmed by surgeon
	Other	Any other complication requiring additional surgery
Infection	Wound	Diagnosis made and confirmed by surgeon
	Severe sepsis	See International Sepsis Definitions Conference [30]

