### Statistical analysis and sample size calculation

A study of the hospital data of one of the participating centers revealed that the number of major complications embedded in the composite primary endpoint was 0.58 per patient, and that a Poisson distribution was applicable. We aim to reduce the number of major complications per patient by 30% (from 0.58 to 0.41). Using Poisson regression with an assumed two-sided error of 5%, we calculated that a sample size of 226 patients in each group will be needed to detect this reduction with a power of 80%. For the multicenter character of the study, a 20% correction was made, since the variance between the participating centers is unknown. This results in a total sample size of 542, or 271 patients in each group.

Statistical analysis will be performed using SPSS version 21.0 for Windows (SPSS Inc, Chicago, Illinois, United States). The first analysis will be performed by combining the results from the participating centers. After this, the results of the individual centers are analyzed to detect possible differences. The primary analysis consists of a comparison of the primary endpoint (number of complications per patient) between the control group and the EGDT group using Poisson regression. According to secondary endpoints, data will be checked for normal distribution and presented as mean +/-standard deviation when normally distributed, and as median +/-interquartile range when not normally distributed. Relative risks are presented with 95% confidence intervals. Categorical data are tested with Fisher’s exact test. Continuous data are tested with the independent samples t-test when normally distributed, and with the Mann-Whitney U test if not normally distributed. A *P* value <0.05 is considered statistically significant. Analysis will be carried out according to the intention-to-treat principle.

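### Death adds only one to an unweighted count and ends further counting, so the count does not reflect severity for death; the stated length-of-stay tests likewise score an early death as a good stay

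*Protocol article*

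**What the plan says.** The Outcome measures section of the protocol article defines the endpoint: "The primary outcome measure is the number of major complications per patient within the first 30 days after surgery, including mortality". Table 2 lists the items. One of its 14 rows is death, with the criterion "Mortality within the first 30 days after surgery". It carries no more weight than the row for wound infection.

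The Primary endpoint section of the Discussion explains why the number of complications was preferred to the proportion of patients with at least one: "In this way, the severity of the complication is reflected". Its example is a patient with pneumonia treated on the ward, who scores one. The contrast is a sicker patient: "If the patient however needs ICU readmission because of respiratory failure and septic shock, three complications are registered". The same section promises separate reporting of each complication and weighting by the Accordion severity score, which Outcome measures lists as a secondary outcome.

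Length of stay in the hospital and in the ICU/PACU is secondary. The statistical section fixes the test for it along with other continuous data: "Continuous data are tested with the independent samples t-test when normally distributed, and with the Mann-Whitney U test if not normally distributed". Analysis is by intention to treat. The Discharge criteria section adds fit-for-discharge definitions to deal with bed capacity, home arrangements and the timing of discharge. Death is not mentioned there.

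**The concern.** Death is both an item in the count and the event that ends counting. A patient who dies early with nothing else on the list scores 1. A survivor with pneumonia and a wound infection scores 2, and the article's example of a severe course scores 3. For the worst outcome, the order is reversed.

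Length of stay has the same structure. If days stayed are compared directly, a patient who dies on day 3 has one of the shortest stays, and a short stay is read as a good result.

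At stake is how the trial is read if mortality differs between arms. More early deaths could make the EGDT arm look somewhat better on either measure than it is. Conversely, if EGDT saves lives, the survivors' later complications and long stays would hide part of the benefit.

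**Working it through.** **Inputs from the article.** The control mean is 0.58 ("the number of major complications embedded in the composite primary endpoint was 0.58 per patient, and that a Poisson distribution was applicable"). The target is a 30% reduction, to 0.41. There are 271 patients per group. On deaths, the Background says "mortality in this specific patient group is around 5" percent.

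**The plan's own figures.** 0.58 × 0.70 = 0.406, given as 0.41, so the target difference is 0.58 − 0.41 = 0.17. The sample size reproduces with the log rate ratio and the null variance in the alpha term: [1.96 × √(2/0.58) + 0.84 × √(1/0.58 + 1/0.406)]² / [ln(1/0.7)]² ≈ 226 per group, and 226 × 2 × 1.2 = 542.4, given as 542. This point does not touch that calculation.

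**Effect on the count.** Let d be the excess share of one arm that dies early with no other listed event, and m the count those patients would otherwise have had. The change in the arm mean is d × (1 − m). With d = 0.02 (an assumption; about 5 of 271 patients):

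| m | Change in mean | Share of 0.17 |
|---|---|---|
| 0 | +0.02 | 12%, toward harm |
| 1 | 0 | 0 |
| 2 | −0.02 | 12%, toward benefit |
| 3 | −0.04 | 24%, toward benefit |

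- Against an average patient the count rises: with 5% excess deaths, 0.95 × 0.58 + 0.05 × 1 = 0.601.
- Under a Poisson distribution with mean 0.58, 11.5% of patients score 2 or more and 2.1% score 3 or more.
- To produce the whole difference of 0.17 by this route, the excess of early deaths would have to be 0.17/(m − 1): 17% at m = 2, 8.5% at m = 3 and 5.7% at m = 4. Total expected mortality is about 5%.

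**Effect on length of stay.** The null standard error of the Mann-Whitney probability with 271 per group is √[(2 × 271 + 1)/(12 × 271²)] = 0.0248. Moving 1% of one arm from an average rank to the shortest shifts the probability by 0.01 × 0.5 = 0.005, and 0.005/0.0248 = 0.2 standard errors. Moving the same 1% from the longest rank to the shortest shifts it by 0.01, or 0.4 standard errors.

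As a cross-check, 1,500 trials were simulated per scenario under assumptions not in the article: log-normal stay with median 12 days and log standard deviation 0.6, deaths on days 1 to 5, and 5% control mortality. A significantly shorter stay in the arm with more deaths appeared in about 2% of trials with equal mortality, 17% with 5 points more deaths and 48% with 10 points more. The approximation agrees at 5 points: the shift is 5 × 0.005/0.0248 = 1.0 standard error, and Φ(1.0 − 1.96) ≈ 0.17.

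**The case against.** The strongest case against has four parts.

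- **The severity sentence has a narrower purpose.** It compares a count with a yes/no endpoint, using non-fatal courses, and does not say that death is ranked worst. That is fair as to intent. As written, though, the sentence covers a composite that includes death, and for death it is wrong.
- **The direction is not fixed.** A reader might infer that early death lowers the primary count, so that the endpoint generally rewards an arm with more deaths. The article does not support this. Death itself adds 1, which is above the planned mean of 0.58. The count falls only for patients who would otherwise have scored 2 or more. Many deaths will also follow another listed event, such as cardiac arrest, respiratory failure or severe sepsis, and then score at least 2.
- **There are safeguards.** Components are reported separately, Accordion grading is planned, deaths are reported immediately, and the DSMB can stop recruitment for harm. Excess deaths would therefore be seen. But about 14 deaths per arm are expected (0.05 × 271), and the article says a mortality comparison would need more than 5,000 patients, so an opposing trend would be visible without being resolved. None of the safeguards changes how either comparison scores death.
- **A death rule for length of stay may stand elsewhere.** The full protocol, the analysis plan and the additional file with the fit-for-discharge criteria are not shown, so the absence of a rule is not in itself a fault. What the article does fix is a plain two-sample test, together with a list of distortions to correct that leaves out death.

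A reader might also infer that the trial will claim benefit from a shorter stay. The article rests its primary conclusion on the count alone.

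**Conclusion.** The point holds in a limited form. The statement that the count reflects severity is not true for death: an isolated early death scores better than survival with two or more complications.

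The consequence for the primary result is probably a modest distortion. For 2% excess early deaths it runs from +0.02 to −0.04 on a target of 0.17, and the sign depends on an unknown m. The −0.04 end assumes that all these deaths are early, that none has another listed event, and that every one of these patients would otherwise have scored 3.

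The stated tests, applied to days stayed, score early deaths as good stays, by 0.2 to 0.4 standard errors per percentage point of mortality difference. That range assumes the deaths fall among the shortest stays. Later deaths shift it less. So may deaths in the ICU/PACU, because the article says most patients leave that unit the morning after surgery. The primary endpoint and the sample size of 542 stand.

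**What to change.** - **Primary endpoint:** keep the count and its Poisson regression. Prespecify one supportive analysis that ranks death by day 30 as worst and survivors by their count, using a rank test stratified by center and type of surgery. Show it, with mortality by arm, beside the primary result.
- **Severity sentence:** in the Primary endpoint section, limit the statement to non-fatal complications and say that death counts as one item.
- **Length of stay:** analyze time to discharge alive with death as a competing event. Alternatively, keep the Mann-Whitney test and give in-hospital deaths the worst rank. Apply the same rule to ICU/PACU stay and to the fit-for-discharge versions. Actual days used can still feed the cost analysis. If the full protocol already has such a rule, a cross-reference is enough.

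The cost is one extra analysis of data already collected, and a length-of-stay result slightly harder to present than a plain median. No extra patients or data items are needed.
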